Eligible patients will provide informed consent and complete the baseline assessments.

The outcome measures are assessed at baseline (T0), again following treatment at 2 months (T1), and then 6 months (26 weeks) after treatment started (T2). The outcome measures are described in detail in the following pages.

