#### Outcome measures

A range of primary, secondary, and tertiary outcome measures (all outlined in the following, see Fig. 2) will be administered at baseline (T0), post treatment (T1, at 10 weeks), and at 6-month follow-up (T2). After T2, participants will be invited to engage in a semi-structured interview (see Subjective experiences of EMDR: qualitative data collection) to gather data on their subjective experience of PTSD and EMDR.

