Health condition(s) or problem(s) studied	PTSD in people receiving care from forensic mental health services
Intervention(s)	EMDR therapy
Key inclusion and exclusion criteria	Inclusion criteria: aged 18–65 years; a lifetime history of a psychotic disorder or a mood disorder with psychotic features as diagnosed according to ICD-10 or DSM-5 criteria; meeting diagnostic criteria for PTSD (Clinician Administered PTSD Scale (CAPS)); current patient of the forensic and rehabilitation mental health services; competent to provide informed consent; likely to remain in the area for the 6-month trial duration (i.e., if a prisoner, release date at least 6 months away; if a patient within a forensic mental health service, their anticipated discharge is at least 6 months away) Exclusion criteria: high suicidality, operationalized as the combination of having a high suicidality score on the Mini International Neuropsychiatric Interview (MINI-plus) or with a suicide attempt within the past 6 months; mental state considered by the treating psychiatrist as too unstable to participate in the trial (participants may be experiencing chronic low-grade symptoms, but cannot be acutely psychotic); insufficient competence in the English language to understand, provide informed consent, and participate in therapy and data collection
Study type	Single-blind, randomized controlled trial
Date of first enrolment	25 May 2018
Target sample size	46
Recruitment status	Currently recruiting
Primary outcome(s)	Change in PTSD symptoms (measured by the CAPS and PSS-SR), treatment safety (measured by the adverse event questionnaire), and acceptability of the EMDR treatment (measured by the TAAS and by qualitative participant feedback)
Key secondary outcomes	Posttraumatic cognitions (PTCI), self-disturbance (TSI-2 Factor 1), posttraumatic stress (TSI-2 Factor 2), externalization (TSI-2 Factor 3), somatization (TSI-2 Factor 4), depression (BDI-II), psychosis (PSYRATS), overall functioning (WHODAS 2.0), social functioning (Social Functioning scale), self-esteem (RSES)

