Secondly, the Posttraumatic Stress Disorder Symptom Scale—Self-Report (PSS-SR) [38] will be administered to assess self-reported severity of PTSD symptoms [39]. The PSS-SR consists of 17 items corresponding to the 17 diagnostic DSM-IV-TR criteria of PTSD which are rated on a 3-point Likert scale, where 0 = *not at all*, 1 = *a little* bit, 2 = *somewhat*, and 3 = *very much*. This yields a total score measuring symptom severity (range 0–51), as well as separate severity scores for re-experiencing (range 0–15), avoidance (range 0–21), and arousal (range 0–15). The PSS-SR will also be administered at T0, T1, and T2, as well as before each treatment session, to assess changes in the PTSD symptoms during treatment. The PSS-SR has revealed satisfactory internal consistency (Cronbach’s α = 0.91), high test–retest reliability (*r* = 0.74), and good concurrent validity (sensitivity = 62%, positive predictive power = 100%, negative predictive power = 82% [38, 40]).

Two primary outcome measures pertain to adverse events. The Adverse Events Questionnaire (AEQ), which we have designed using similar questions to Van den Berg et al. [16], is a checklist that will help establish treatment safety. In 10 questions, the patient is asked to report any experiences they have had over the last 2 months of self-harm, suicide attempt, deliberately hurting another person, excessive use of alcohol, excessive use of drugs, having needed help because of a crisis, moving back to a higher level of security within the services, or any reoffending.

The Adverse Events Session Rating scale will also be used to assess adverse events in the participant before and after treatment sessions (sessions two and three), for example, being suicidal and hearing voices. Participants will respond on a 10-point visual analog scale (from “*no, not at all*” to “*yes, very much*”) to the questions.

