### Trial monitoring and oversight

The risks of the study are thought to be low based on previous research, which has found EMDR to be safe, effective, and well tolerated in people with serious mental illness. However, the population is vulnerable so there are a number of safeguards in place. A Data Monitoring Committee (DMC) has been set up as an advisory body responsible for monitoring emerging safety and efficacy data, reviewing trial conduct and making recommendations. The DMC is independent of the study organizers and funders. Its membership is multidisciplinary and comprises the Clinical Director (Chair) and Operations Manager from the Central Regional Forensic and Rehabilitation Service, a senior psychologist not related to the study, and the principal investigator. During the recruitment period, interim analyses will be supplied in strict confidence to the DMC, together with any analyses the DMC may request.

The base rate of serious events in this population is much higher than in the general population, and it may be difficult to establish whether such events are related or unrelated to therapy. All serious adverse outcomes will be reported immediately to the DMC. We have predetermined that any serious event such as a serious deliberate self-harm attempt (requiring medical attention), an assault on another person (requiring medical attention), or a return to an environment of high security will be a reason for the participant being withdrawn from the study. Any other significant adverse effects will be discussed on a case-by-case basis. The DMC and research team will formally review the feasibility and safety of the study after data have been collected on 10 participants, before further participants are recruited.

The terms of reference of the DMC are available on request from the principal investigator.

In the unlikely event that someone is harmed in the course of the trial, they would be eligible under New Zealand law to apply for compensation from the Accident Compensation Corporation. This is explained in the informed consent process.

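### The primary safety questionnaire looks back 2 months but is given at 10 and 26 weeks, so on the visible schedule about a third of follow-up is not asked about

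*Protocol article*

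**What the plan says.** Under the heading on primary outcome measurements, the protocol states "Two primary outcome measures pertain to adverse events". The first is the AEQ, a study-made checklist of 10 questions that asks patients to "report any experiences they have had over the last 2 months of self-harm, suicide attempt, deliberately hurting another person". It goes on to excessive alcohol, excessive drug use, help needed in a crisis, a return to higher security and reoffending. The second is a session rating scale, used "before and after treatment sessions (sessions two and three"). Table 2, the registration data set, names only the AEQ for this outcome: "treatment safety (measured by the adverse event questionnaire").

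The Outcome measures section says that the primary, secondary and tertiary measures "will be administered at baseline (T0), post treatment (T1, at 10 weeks), and at 6-month follow-up (T2"). The Recruitment section puts the visits differently: "again following treatment at 2 months (T1), and then 6 months (26 weeks) after treatment started (T2"). The text below Fig. 2 makes T2 the point at which the waiting list begins its treatment.

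Trial monitoring and oversight adds a separate route: "All serious adverse outcomes will be reported immediately to the DMC". Its examples are self-harm or assault needing medical attention and a return to high security.

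**The concern.** A fixed look-back covers follow-up only if the visits are no further apart than the look-back is long. Here they are 10 and then 16 weeks apart, against a look-back of about 8.7 weeks. Events in the remainder are not asked about, and no later analysis can recover them.

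Safety is part of the primary aim. The session rating scale cannot stand in for the AEQ: it is tied to two treatment sessions, so it has no counterpart on the waiting list and sees nothing after therapy. The longer part of the gap comes soon after a nine-session weekly course would end, which is a period in which one would look for delayed effects.

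The visit times are also not fixed in one way. T1 is given as 2 months in the Recruitment section and as 10 weeks in the Abstract and under Outcome measures. T2 is counted from the start of treatment, an event that the waiting list does not have before T2.

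**Working it through.** The plan states no coverage figure, so there is none to reproduce.

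**Inputs**
- Look-back *w*: 2 months (AEQ description). Converted, 365.25/12 × 2 / 7 = 8.70 weeks. Alternatives: 8 weeks, 60 days (8.57 weeks), 9 weeks.
- T1: week 10 (Outcome measures), or 2 months (Recruitment).
- T2: week 26 (Recruitment).

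**Formula.** Covered time is [T1 − w, T1] plus [T2 − w, T2]. As long as *w* is no longer than either interval between visits, the uncovered time is 26 − 2w, whatever T1 is.

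**Main case, T1 at week 10, w = 8.70**
- Covered: weeks 1.3 to 10 and 17.3 to 26, that is 2 × 8.70 = 17.4 weeks.
- Uncovered before T1: 10 − 8.70 = 1.3 weeks.
- Uncovered between T1 and T2: 16 − 8.70 = 7.3 weeks, 7.3/16 = 46% of that interval.
- Total: 8.6 weeks, 8.6/26 = 33.1%.

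**Range over conversions, T1 at week 10**

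| w (weeks) | before T1 | T1 to T2 | total | share of 26 |
|---|---|---|---|---|
| 8 | 2.0 | 8.0 | 10.0 | 38.5% |
| 8.57 | 1.4 | 7.4 | 8.9 | 34.1% |
| 8.70 | 1.3 | 7.3 | 8.6 | 33.1% |
| 9 | 1.0 | 7.0 | 8.0 | 30.8% |

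**T1 at 2 months.** The total stays at 8.6 weeks (33.1%), now all between T1 and T2: 8.6/17.3 = 50% of that interval. The finding does not depend on which T1 is meant.

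**What is lost.** At a constant event rate, 33% of events fall in the gap. The proportion of participants with any event loses less. If a proportion *p* would have an event in 26 weeks, the proportion seen is 1 − (1 − p)^(17.4/26), with 17.4/26 = 0.669. Two assumed values of *p*, for illustration only:
- p = 50%: 1 − 0.5^0.669 = 37%, a loss of 26% of those participants.
- p = 80%: 1 − 0.2^0.669 = 66%, a loss of 18%.

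The loss approaches one third for rare events and is smaller for recurring behaviour.

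**Effect of the anchor.** If both visits are counted from treatment start and therapy begins an assumed 2 weeks after T0, follow-up from T0 is 28 weeks and the uncovered time is 28 − 17.4 = 10.6 weeks (38%).

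**After the fix.** Asking about the time since the previous assessment covers 10 + 16 = 26 of 26 weeks.

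**The case against.** The strongest case on the other side has five parts.

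- *The AEQ schedule is read from a general sentence.* The visit grid is Fig. 2, whose legend lists the AEQ but which is not shown, and the form itself is not shown. An extra administration cannot be ruled out. This stands as a limit. However, the sentence that cites Fig. 2 gives only three time points, and no visible text gives a longer look-back at T2.
- *Serious harm is captured elsewhere.* This stands. A reader might infer that delayed harm after therapy goes unrecorded altogether. The documents do not support that, because immediate reporting to the committee has no recall window. What has no other stated source is the non-serious content.
- *The early gap is small and may be loose wording.* This largely stands. With T1 at 2 months there is no gap before T1. The first session is assessment and planning, so if therapy starts promptly the T1 window covers nearly all active treatment. Nine weekly sessions would then end at about week 9, so the later gap opens soon after therapy ends, not at that moment.
- *An equal look-back is defensible.* It keeps T0, T1 and T2 comparable and avoids a 16-week recall in people with psychotic illness. Recruitment began in May 2018, so replacing the question would mix windows within the trial. This is a good reason to add a question and not to replace the existing one.
- *The gap is the same in both arms.* This stands. A reader might infer a biased comparison, but bias would need event timing to differ by arm, which is possible around the end of therapy and is not shown. Nor do the documents show that the EMDR arm is measured later at T2; the wording only allows it.

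**Conclusion.** The concern holds as a coverage gap in a primary outcome. On the visible schedule about 8.6 of 26 weeks (33%; 31% to 38% across conversions) lie outside any AEQ window, mainly weeks 10 to 17.3. The sure consequence is under-counting and loss of information on non-serious self-harm, excessive alcohol or drug use and crisis help, in both arms alike.

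The size rests on two assumptions: that the AEQ is given only at T0, T1 and T2, and that the look-back is applied as written. The figure of one third of events also assumes a constant rate; if events cluster soon after week 10, more would be missed. It should not be read as one third of participants with an event, for whom it is an upper limit under that same assumption. The documents give no event rate, so no effect on power can be stated; the sample size was set on the CAPS.

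The conflict over T1 and the missing anchor for T2 in the waiting list are separate, real and easily corrected.

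**What to change.** - Keep the 2-month question at T0, T1 and T2, for comparability with baseline and with data already collected.
- At T1 and T2 add the same items, asked *since your last study assessment*.
- Compare arms on events from T0 to T1 and from T0 to T2, using the added items.
- Reconcile the Recruitment section with the Abstract and Outcome measures on when T1 falls, and count T1 and T2 from randomization in both arms.
- If Fig. 2 already provides another AEQ administration, say so in the text.

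The cost is a slightly longer form, a 16-week recall at T2 and a small protocol amendment. No validated instrument is altered, because the AEQ was made for this study. Participants already assessed will have only the 2-month data, so the report should state how many that is and give the 2-month results for everyone beside the full-interval results.

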## Study aims

### Primary aim

In a sample of people receiving forensic and rehabilitation mental health care, we aim to examine: the efficacy of EMDR versus the waiting list for treating PTSD symptomology; and the safety and acceptability of EMDR versus the waiting list as indicated by adverse events.

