#### Experimental intervention: EMDR

In addition to treatment as usual, the participants randomized to EMDR will undergo nine sessions of EMDR therapy, each 60-min long. The first session will involve assessment and planning, and the subsequent eight sessions will involve active EMDR treatment.

In the first session, the treatment rationale will be explained. The therapist will receive information from the Interview for Traumatic Events in Childhood (ITEC), a reliable and valid tool for assessing early traumas [35]. The ITEC captures categories (e.g., sexual abuse, physical abuse) of experienced traumatic events. In addition, the intensity of re-experiencing symptoms of each traumatic event is assessed. Based on the ITEC, the therapist draws up a preliminary, formatted EMDR case conceptualization (when crucial memories are identified for reprocessing [36]), which they discuss and complete together with the patient in the first session. This results in a hierarchy of the most relevant traumatic memories in order of significance with regard to the symptoms of PTSD.

During the next eight sessions, the identified traumatic memories will be processed following the basic EMDR protocol. The participant is asked to focus on the currently most distressing image of a memory in a multimodal manner, including its image, thought (an experienced negative cognition (NC) and a healthier positive cognition (PC)), emotion, physical sensation, and level of tension. The patient then rates this memory on a subjective unit of distress (SUD) scale from 0 to 100. Processing of the memory starts when the therapist asks the patient to hold the target image in mind while concentrating on a distracting stimulus (the finger of the therapist eliciting eye movements) for about 30 s. The patient reports briefly what comes to mind and is guided by the clinician to refocus on that element while focusing on the distracting stimulus. This continues until no more associations come up and the disturbance level associated with the target memory (SUD) drops to zero.

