#### Primary outcome measurements: PTSD symptoms, adverse events, and treatment acceptability

There are two primary outcome measures pertaining to PTSD symptoms, two regarding treatment safety, and one measure of the acceptability of EMDR treatment. The first primary outcome measure is the CAPS, which is a 30-item structured interview that assesses DSM-5 PTSD symptoms [37]. The CAPS will be used to assess the presence or absence of PTSD diagnosis and the frequency and intensity of the clinician-rated PTSD symptoms.

**Table 1 Tab1:** Secondary outcome measures

Secondary outcome	Measurement instrument^a^	T0	T1	T2
Posttraumatic cognitions	PTCI (s)	X	X	X
Self-disturbance	TSI-2 Factor 1 (s)	X	X	X
Posttraumatic stress	TSI-2 Factor 2 (s)	X	X	X
Externalization	TSI-2 Factor 3 (s)	X	X	X
Somatization	TSI-2 Factor 4 (s)	X	X	X
Depression	BDI-II (s)	X	X	X
Psychosis	PSYRATS (i)	X	X	X
Overall functioning	WHODAS 2.0 (i)	X	X	X
Social functioning	Social Functioning Scale (i)	X	X	X
Self-esteem	RSES (s)	X	X	X

^a^ (i) = measurement interview, (s) = self-report

BDI-II, Beck Depression Inventory—second edition; PTCI, Posttraumatic Cognitions Inventory; PSYRATS, Psychotic Symptom Rating Scales; RSES, Rosenberg Self-Esteem Scale; T0, baseline; T1, post treatment; T2, 6-month follow-up; TSI-2, Trauma Symptom Inventory—second edition; WHODAS, World Health Organization Disability Assessment Scale

**Table 2 Tab2:** Items from the World Health Organization Trial Registration Data Set

Data category	Information
Primary registry and trial identifying number	Australia and New Zealand Clinical Trials Network, registration number ACTRN12618000683235 (registered prospectively)
Date of registration in primary registry	26 April 2018
Sponsor	University of Otago Contact details: Office of Research and Enterprise, Otago University, [name]. Tel. [name]
Contact for public/scientific queries	[contact]
Public title	Eye movement desensitization and reprocessing (EMDR) therapy for posttraumatic stress disorder in adults with serious mental illness within forensic and rehabilitation services: a study protocol for a randomized controlled trial
Scientific title	Eye movement desensitization and reprocessing (EMDR) therapy for posttraumatic stress disorder in adults with serious mental illness within forensic and rehabilitation services: a study protocol for a randomized controlled trial
Countries of recruitment	New Zealand

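### The session-level primary safety rating stops after the first two of eight active EMDR sessions, so a brief, non-serious worsening of suicidality or voices around sessions four to nine has no scheduled rating

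*Protocol article*

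**What the plan says.** The section on primary outcome measurements sets out the count: "There are two primary outcome measures pertaining to PTSD symptoms, two regarding treatment safety, and one measure of the acceptability of EMDR treatment". The two safety measures are the AEQ and the Adverse Events Session Rating scale.

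- **AEQ.** This is a ten-question recall checklist in which "the patient is asked to report any experiences they have had over the last 2 months of self-harm, suicide attempt, deliberately hurting another person", followed by substance use, crisis help, return to higher security and reoffending.
- **Session Rating scale.** "The Adverse Events Session Rating scale will also be used to assess adverse events in the participant before and after treatment sessions (sessions two and"; the list ends at session three. The examples given are being suicidal and hearing voices, each answered on a 10-point visual analog scale.

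The section on the experimental intervention gives the treatment course: "the participants randomized to EMDR will undergo nine sessions of EMDR therapy, each 60-min long". It divides them as follows: "The first session will involve assessment and planning, and the subsequent eight sessions will involve active EMDR treatment".

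The PTSD self-report is the one questionnaire that the text gives throughout treatment: "The PSS-SR will also be administered at T0, T1, and T2, as well as before each treatment session".

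**The concern.** A rating taken immediately before and after a session exists to catch short-lived reactions that a later recall questionnaire or a follow-up interview may miss. Here it is confined to the first two sessions of memory processing. The intervention section describes a hierarchy of traumatic memories worked through over all eight active sessions. Early completion requires the distress score to reach zero on every situation in the case conceptualization, so treatment is expected to move on to further targets after session three. The protocol gives no reason for stopping the rating there.

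What is at stake is how far a descriptive safety statement can reach. If the report says that sessions were not followed by worsening of suicidality or voices, that statement will come from sessions two and three. Ratings that were never taken cannot be recovered in the analysis, so this is settled by the schedule and not by an analysis plan.

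**Working it through.** **1. Coverage of the session scale.** Inputs, from the intervention and primary outcome sections: nine sessions, one for planning, eight active, two rated.

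- Active sessions: 9 − 1 = 8, numbered two to nine. This agrees with the protocol's own count.
- Rated: 2/8 = 25%. Not rated: 6/8 = 75%.
- Over an EMDR arm of 23, with every session attended (assumption): 23 × 2 = 46 rated sessions of 23 × 8 = 184 active sessions.

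**2. Whether another instrument rates the same reactions around sessions four to nine.**

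| Instrument | When | What it leaves open |
|---|---|---|
| AEQ | T0, T1, T2; two-month recall | Retrospective; the experiences listed are events and behaviours |
| PSYRATS (voices, delusions) | T0, T1, T2 | A reaction that has resolved by T1 |
| TSI-2 (has a suicidality subscale) | T0, T1, T2 | The same |
| PSS-SR | T0, T1, T2 and before each session | Covers the 17 PTSD criteria only |
| SUD | During processing | Rates the distress of the target memory |
| Serious event reporting to the DMC | As events occur | Anything short of serious |

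None is a scheduled before-and-after rating of suicidality or voices at sessions four to nine.

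**3. What the AEQ does reach.** The outcome measures "will be administered at baseline (T0), post treatment (T1, at 10 weeks), and at 6-month follow-up (T2").

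- Two months in weeks: 2 × 365.25 / 12 / 7 = 8.7.
- With T1 at week 10, the recall window opens at week 10 − 8.7 = 1.3.
- Weekly sessions starting in week 0 (assumption): session two falls in week 1 and is outside; sessions three to nine are inside. That is 7 of 8 active sessions.
- Weekly sessions starting in week 1 (assumption): sessions two to nine are inside. That is 8 of 8.

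Under either start, sessions four to nine all lie inside the AEQ window. The gap is therefore limited to reactions that the AEQ does not elicit, that are not serious, and that have passed by T1.

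**4. Which measure answers the safety aim.** The primary aim is comparative: "the safety and acceptability of EMDR versus the waiting list as indicated by adverse events". The text under Fig. 2 places within-session assessments in the EMDR group and starts the waiting-list group's treatment at T2. The session scale therefore has no control-arm counterpart, whether it is given at two sessions or at eight. Table 2 names only the AEQ for treatment safety.

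**The case against.** The strongest reply is that the timing is clearly stated and defensible. The memory hierarchy is ordered by significance, so the first two processing sessions may well carry the main targets, and rating first exposure is a coherent choice. Nothing in the documents shows that risk concentrates later. If the per-session risk were constant, sessions two and three would estimate it without bias and only precision would be lost. Further ratings would add uncontrolled EMDR-arm data at some burden. The AEQ is also said to have ten questions while the text names eight experiences, so one cannot say from the article that it has no item on suicidal thoughts or voices.

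Much of this stands, and it keeps the point small. It does not remove it: the protocol makes this scale a primary safety measure, does not state that reactions are confined to early sessions, and schedules nothing equivalent afterwards. Whether risk is constant across sessions is something that two early sessions cannot show.

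Three stronger readings are tempting and not supported:

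- A reader might infer that the risk-of-harm aim is answered from a quarter of the treatment exposure. It is not. That aim compares arms and rests on the AEQ, whose T1 window takes in 7 or 8 of the 8 active sessions.
- A reader might infer that suicidality and voices are never measured after session three. They are: PSYRATS and the TSI-2 are taken at T1 and T2, the AEQ asks about self-harm, suicide attempts and crisis help, and serious events go to the DMC at once. Only the immediate before-to-after change is missing.
- A reader might want a figure for the chance of missing an episode. The documents give no per-session rate and no definition of a marked worsening, so any such figure would rest on invented inputs.

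**Conclusion.** The point holds, as a minor one. One of the two primary safety measures samples the first 2 of 8 active sessions. For the other six, worsening of suicidality or voices has no scheduled rating when it meets three conditions together: it is not a serious event, it is not captured by the AEQ's two-month recall, and it resolves before T1. The between-arm safety comparison, the sample size and the power are untouched.

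The session count is read directly from the text and needs no assumption. The AEQ coverage assumes T1 at 10 weeks and weekly sessions beginning in week 0 or week 1. How often the unrated reactions would occur cannot be estimated from the documents.

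**What to change.** In the primary outcome section, replace the restriction to sessions two and three with every active session attended, that is, sessions two to nine. The pre-session rating can be taken with the PSS-SR, which is already given at that moment; the post-session rating is a few visual analog items. Report for each participant the largest before-to-after worsening and the number of sessions with any worsening, labelled as descriptive data from the EMDR arm.

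The cost is a few minutes of participant time at up to six more sessions, fewer for early completers, with no extra visits or staff. Coverage rises from 2/8 to 8/8 of the active sessions attended.

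If the present schedule is kept, state that any conclusion on session-related worsening applies to sessions two and three only.
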